#### Sample size requirements

This study is powered at country level and is based on the 95% CIs around the limits of agreement for each of the respective analyses are within ±10% of the values from previous studies. A total of 290 women are needed to achieve a minimum of 10% precision, meaning the sample size for objectives #1 and #2 must each be at least 290 women. Each country will recruit until these targets are met. Assuming a 10% loss to follow-up between the first and second trimesters, each country will aim to recruit 323 women. We estimate the multicountry dataset will comprise 969 women.

#### Analysis

Baseline characteristics of study participants will be described using means and SDs for normally distributed variables, medians and 25th and 75th percentiles for non-normally distributed variables and frequencies and percentages for binary and categorical variables.

Analysis for objectives 1, 2 and 3 will estimate (with 95% CIs) the mean difference and 95% limits of agreement between the gestational age estimates by IU and CRL (objective 1), ‘extrapolated CRL’ (objective 2) or fetal biometry (objective 3). Extrapolated CRL is the CRL-estimated gestational age plus the time difference (in days) between an individual’s first (Visit 1) and second trimester (Visit 2) measurement dates. The mean difference and 95% limits of agreement will be displayed with their 95% CIs within a Bland-Altman style plot of the mean differences (y-axis) and average estimated gestational age (x-axis). In addition, fixed and proportional bias between gestational age estimates obtained using conventional ultrasound and the IU device will be evaluated using reduced major axis regression (RMAR).^24^ RMAR provides the slope and intercept of the regression line. A slope different from one indicates proportional bias, meaning that the magnitude of the difference between gestational age measured by conventional ultrasound and IU device varies with the magnitude of the conventional ultrasound measurements. If no proportional bias is present, an intercept different from 0 indicates fixed bias, meaning the difference between the two gestational age measurement methods remains consistent across the range of conventional ultrasound gestational age estimates.

Analysis of objective 4 will estimate (with 95% CIs) the measures of diagnostic performance (specifically the detection rate and the false positive rate) of the IU gestational age estimation approach for classifying individuals as less than 20 weeks’ gestation, compared with conventional ultrasound fetal biometry, both measured at the second trimester, as binomial proportions. The complete data analysis plan is described in online supplemental appendix B.

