### Rationale for a prospective cohort study on AI-based gestational age estimation in sub-Saharan Africa

Implementing an AI-based ultrasound will introduce new challenges for health services. While some women in Ghana, Kenya and South Africa will have had a conventional ultrasound prior to being screened for eligibility to the study, approximately just under a half to three-quarters of women will not, based on PEARLS site investigators’ estimates. Potential benefits of this AI-based ultrasound system for PEARLS include:

AI-based ultrasound can be performed by a health worker with minimal (rather than specialist) training, so gestational age estimation can be scaled up more quickly and easily.The gestational age estimate is generated by the software immediately and does not require expert review or interpretation.The IU ScanNav FetalCheck system uses GE’s handheld, point-of-care ultrasound device. The latter is commercially available, and has previously received regulatory approval in Ghana, Kenya, South Africa and many other countries.The hand-held, point of care ultrasound device allows easy transit between multiple sites, and the smaller size means it can be used in multipurpose clinical areas.

The algorithm underpinning this functionality has been trained on a retrospective dataset of over 2 million antenatal ultrasound images from over 75 000 pregnant women, obtained from centres in Australia, India and the UK.^18^ It has been validated in silico (retrospective computer-based validation) using a separate retrospective validation dataset of over 700 patients, also from Australia, India and the UK. These studies showed the AI-based algorithm showed a mean absolute error of 1.7 days between 14 and 18 weeks gestational age and 2.8 days between 18 and 24 weeks, outperforming traditional fetal biometry.^18^

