**Figure 2 F2:**

Flow of participants in the AI ultrasound validation study. AC, abdominal circumference; AI, artificial intelligence; BPD, biparietal diameter; CRL, crown-rump length; FL, femur length; HC, head circumference; IU, intelligent ultrasound; LMP, last menstrual period; USS, ultrasound scan.

Women will be invited to return during the second trimester for Visit #2, at a randomly selected gestational age, between 14^+0^ and 27^+6^ weeks. The timing of Visit #2 is generated randomly in REDCap at the end of Visit #1. During Visit #2, the participant will again receive a conventional ultrasound, performed by a study sonographer. Again, the viability of the fetus will be confirmed via conventional ultrasound and any detected anomalies reported. Fetal biometry measurements will be obtained of the HC, BPD, AC and FL with the images and measurements uploaded directly to REDCap as well as a gestational age estimate according to the second trimester scan (by HC). Immediately after, a research midwife will perform a series of abdominal sweeps using the IU system and the gestational age output will be entered into REDCap. A detailed description of the operational definitions of outcomes is included in online supplemental appendix B, table 1. Where women cannot attend or miss their randomised appointment date (Visit #2, allocated to a 7-day period), women will be invited to attend at the closest available dates, as long as it is before 28 weeks.

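### For objectives 2 and 3 one pair of limits of agreement spans 14+0 to 27+6 weeks, although the protocol's own in-silico errors suggest that spread grows with gestation; gestation-specific limits should be added

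*Protocol article*

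**What the plan says.** The Analysis section of the protocol article treats objectives 1, 2 and 3 alike. It "will estimate (with 95% CIs) the mean difference and 95% limits of agreement between the gestational age estimates", and then: "The mean difference and 95% limits of agreement will be displayed with their 95% CIs within a Bland-Altman style plot". No limits by gestational band, no limits that vary with gestation and no check for changing spread are stated there. The one stated check on dependence on gestation is that "fixed and proportional bias between gestational age estimates obtained using conventional ultrasound and the IU device will be evaluated using reduced major axis regression".

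Under Participant flow and follow-up, Visit 2 takes place "at a randomly selected gestational age, between 14^+0^ and 27^+6^ weeks", so objectives 2 and 3 pool scans from 14 different weeks.

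The rationale section gives the error of this algorithm as a "mean absolute error of 1.7 days between 14 and 18 weeks gestational age and 2.8 days between 18 and 24 weeks". On the origin of those figures it says: "It has been validated in silico (retrospective computer-based validation) using a separate retrospective validation dataset of over 700 patients".

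Under Sample size requirements, the target is that "95% CIs around the limits of agreement for each of the respective analyses are within ±10% of the values from previous studies".

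**The concern.** Limits of agreement built from one standard deviation describe individual women correctly only if the differences have the same spread at every gestation. The protocol's own evidence points the other way for this device. By design, the second visit mixes early and late scans, so the pooled standard deviation averages unlike error distributions. The resulting interval would then be too wide where the device is most precise and too narrow where it is less precise.

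Objective 2 is a primary objective, and its headline result is this interval. The introduction ties accurate dating to starting aspirin before 20 weeks. The rationale ties reliance on the device to its being at least equivalent to standard care. An interval shaped largely by later scans does not describe performance in the early range, and it would flatter performance in the later documented band.

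**Working it through.** **1. The plan's own figure.** For n pairs with standard deviation s of the differences, Var(limit) = s²[1/n + 1.96²/(2(n−1))]. The half-width of the 95% CI of a limit, relative to the distance 1.96s, is therefore √(1/n + 1.96²/(2(n−1))). At n = 290 this is 10.05%; exactly 10% needs n = 293. The statement "A total of 290 women are needed to achieve a minimum of 10% precision" is thus reproduced. Allowing for 10% loss, 290/0.9 rounds up to 323 per country, and 3 × 323 = 969. The sample size arithmetic is not in question.

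**2. Inputs.** Mean absolute errors (MAE) of 1.7 and 2.8 days come from the rationale section. The ratio is 2.8/1.7 = 1.647, or 65% more. Assumptions: normal errors with zero mean, and a visit week uniform over 14 weeks.

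**3. Limits by band.** SD = MAE × √(π/2).
- 14–18 weeks: 1.7 × 1.2533 = 2.13 days; limits ±1.96 × 2.13 = ±4.2 days.
- 18–24 weeks: 2.8 × 1.2533 = 3.51 days; limits ±6.9 days.

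**4. Pooled limits.** The pooled variance is the week-weighted mean of the band variances. Coverage in a band is 2Φ(L/SD) − 1, where L is the pooled limit.

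| Scenario | Pooled limits | 14–18 weeks | Later |
|---|---|---|---|
| Documented bands only, weights 4:6 | √[(4×2.13² + 6×3.51²)/10] = 3.03; ±5.95 days | 42% too wide, covers 99.5% | 18–24 weeks: 13% too narrow, covers 91.0% |
| Error flat from 18 to 28 weeks, weights 4:10 | √[(4×2.13² + 10×3.51²)/14] = 3.18; ±6.23 days | 49% too wide, covers 99.6% | 18–28 weeks: 9% too narrow, covers 92.4% |

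**5. Added reference error.** Take the flat scenario and add a constant reference SD of 3 days (assumed). The band SDs become √(2.13² + 9) = 3.68 and √(3.51² + 9) = 4.62, a ratio of about 1.25. The pooled SD is √[(4×3.68² + 10×4.62²)/14] = 4.37. Then 4.37/3.68 is 19% too wide early, and 4.37/4.62 is 5% too narrow later.

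**6. 24–28 weeks.** No figure is documented. For an assumed MAE of 3.0 to 4.5 days there, the pooled limits run from ±6.4 to ±7.8 days. They would be 53% to 86% too wide below 18 weeks and 13% to 30% too narrow at 24–28 weeks. At 18–24 weeks they would move from 7% too narrow to 13% too wide.

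**7. Would the planned regression show it?** The reduced major axis slope is the ratio of the two SDs. A uniform window of 98 days has an SD of 98/√12 = 28.3 days. With no mean bias and the flat scenario's error, the slope is √(28.3² + 3.18²)/28.3 = 1.006. In 4,000 simulated studies of 290 women it averaged 1.006, with 95% of runs between 0.994 and 1.019. A slope that close to 1 gives no signal of the changing spread.

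**8. Precision of gestation-specific limits,** by the formula in step 1, on 290 women per country and 870 in all.
- Four-week band: 290 × 4/14 ≈ 83 women, ±19% per country; 870 × 4/14 ≈ 249 women, ±11% across countries.
- Six-week band: 290 × 6/14 ≈ 124 women, ±15% per country; 870 × 6/14 ≈ 373 women, ±9% across countries.

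**The case against.** Several points on the other side are sound.

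- **The evidence is indirect.** The two MAEs are retrospective computer-based results from Australia, India and the UK. The rationale itself says that the system has not been tested prospectively or in African pregnancies. The direction is expected, not known, and turning an MAE into an SD needs a distributional assumption.
- **The contrast may be diluted.** The rationale does not say what the MAE was measured against. Reference error that is the same at all gestations shrinks the effect, as step 5 shows. For objective 3 the comparator is same-visit head circumference, whose error by gestation is not given, so the sizes above are not established for that comparison.
- **The pooled limits are legitimate.** A reader might infer that they rest on an arbitrary mix of weeks and should be demoted. The documents do not support that: the visit week is randomised by design, the objective is defined over the whole window, and the sample size was built on the pooled limits. They are a valid marginal summary, but an incomplete one.
- **The early range has other coverage.** Objective 4 assesses classification at 20 weeks, and the plot would show fanning by eye. But detection and false positive rates do not give the size of the error in days, and a visible fan leaves the reported limits constant.
- **Appendix B is said to hold the complete analysis plan and is not shown.** It may already contain limits by gestation. A reader might infer that the study has no such analysis; that cannot be concluded. The point concerns the analysis the article does state, which addresses dependence on gestation for bias only.

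**Conclusion.** The point holds as an expectation for objectives 2 and 3. Objective 1, with its three-week window, is not affected. If the in-silico pattern carries over, with normal zero-mean errors and a uniform visit week, constant limits would be about 42% too wide at 14–18 weeks and 13% too narrow at 18–24 weeks on the documented bands. If error is flat to 28 weeks the figures are 49% and 9%; with an assumed 3-day reference SD as well, about 19% and 5%. The stated regression would neither reveal nor correct this.

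A reader might go further and say that the limits will certainly overstate performance at 24–28 weeks, by a fifth or more. The documents do not support that: they report no error beyond 24 weeks, and any such size rests on an assumed value. If error stays flat, the late shortfall is 9%, smaller than the ±10% precision the study was planned for. The larger and better documented effect is in the early weeks, where one pooled interval would make the device look less precise than it is.

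**What to change.** Keep the pooled limits for objectives 2 and 3, and add gestation-specific limits to the Analysis section. Either of two methods serves, and both use data already collected:

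- **Regression:** regress the difference on gestational age, regress the absolute residuals on gestational age, and multiply the fitted values of the second regression by √(π/2) to obtain the SD. Report limits at fixed weeks with bootstrap CIs.
- **Bands:** report separate limits for 14+0–17+6, 18+0–23+6 and 24+0–27+6 weeks.

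Base statements about dating before 20 weeks on these limits, not on the pooled pair. If appendix B already contains such an analysis, it is enough to bring the article's Analysis section into line with it.

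The cost is precision. A four-week band has about 83 women per country, with limits known to about ±19%, and about 249 across the three countries, about ±11%. The text should therefore say that the ±10% target applies to the pooled limits only. No change to recruitment or data collection is needed.

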#### Study population

The population eligible for this study are women presenting at a participating facility for an antenatal visit, between 11^+0^ and 13^+6^ weeks gestation. These women can be any age, parity, body mass index and with a singleton or multiple gestation. Pregnant women in whom a major fetal abnormality is known or detected, or where a fetal heart rate cannot be detected, are not eligible.

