#### Recruitment

Women attending the participating facilities will be systematically approached by trained research staff and invited to take part in this study, in conjunction with other PEARLS formative research activities. Women with an estimated gestational age of <16 weeks based on best clinical estimate will be invited for screening. During the pre-screening process, an initial, routine conventional scan (gestational age, fetal heart rate) will be performed to assess eligibility. Those eligible for the study (gestational age 11^+0^ to 13^+6^, fetal heart rate present and no known congenital anomaly) will be invited to participate in the study and informed consent obtained prior to data collection. Women who are not eligible or do not consent to participate will receive the same clinical care they would otherwise receive. Study participants will also continue to receive usual clinical care. If an anomaly or absent fetal heart rate is detected during the study (or any other clinical issues are identified) the participant will be referred for appropriate clinical care.

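### In the 11 to 13 week window the reduced major axis slope confounds random error with proportional bias, so the stated slope and intercept rules can give a wrong bias verdict for objective 1

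*Protocol article*

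**What the plan says.** For objectives 1 to 3 the Analysis section plans the mean difference and 95% limits of agreement, each with 95% CIs, and a Bland-Altman style plot. It then adds reduced major axis regression (RMAR) to evaluate fixed and proportional bias, with two reading rules. On the slope: "A slope different from one indicates proportional bias". On the intercept: "If no proportional bias is present, an intercept different from 0 indicates fixed bias". Neither rule carries a condition on the error variances of the two methods, and the intercept is not centred.

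The range of ages differs greatly between objectives. Under Study population, women are eligible "between 11^+0^ and 13^+6^ weeks gestation". Visit 2 takes place "at a randomly selected gestational age, between 14^+0^ and 27^+6^ weeks". Under Recruitment, "an initial, routine conventional scan (gestational age, fetal heart rate) will be performed to assess eligibility"; Participant flow and follow-up places the Visit 1 scan, with its three CRL measurements, after pre-screening and consent.

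**The concern.** The RMAR slope of IU age on conventional age equals SD(IU)/SD(conventional). It departs from 1 when the scales differ, but also when the scales agree and one method is noisier. It departs from 1 as well when selection caps the spread of one method and not the other. In a 21-day window a few days of random error is a sizeable share of the total SD, so the rule may report proportional bias for a device that has none. Noise can equally offset a true slope below 1 and hide real compression of ages.

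The intercept rule depends on the slope rule, because it is read only when the slope is not flagged. It also refers to a gestational age of 0, far outside the data. The Introduction ties reliance on the device to showing equivalence with standard care, so a published false bias verdict, or a missed one, would mislead that judgement.

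**Working it through.** **The plan's own figure.** The sample size rests on 95% CIs for the limits of agreement within 10%. Taking the CI half-width as 1.96·s·√((1 + 1.96²/2)/n) and setting it to 0.10 × 1.96·s gives n = (1 + 1.9208)/0.01 = 292, close to the stated 290. Then 290/0.9 = 322.2, rounded up to 323, and 3 × 323 = 969. So n = 290 is used below.

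**Inputs**
- Objective 1 window: 21 days. With a uniform spread (assumption), variance = 21²/12 = 36.75, SD = 6.06 days, centre about 87.5 days.
- Visit 2 window: 98 days. If uniform, SD = 98/√12 = 28.3 days.
- IU error: the Introduction gives in-silico mean absolute errors of 1.7 days (14 to 18 weeks) and 2.8 days (18 to 24 weeks). If errors are normal, SD = 1.253 × MAE, i.e. 2.13 and 3.51 days. Carrying these to 11 to 13 weeks is an assumption.
- CRL error: not given. Values of 0, 1.5 and 2.0 days are tried.

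**Expected slope for an unbiased IU.** If the window does not depend on the CRL error, slope = √[(36.75 + var IU error)/(36.75 + var CRL error)]. With an error-free CRL:
- IU SD 2.13: √(1 + 4.54/36.75) = 1.06
- IU SD 3.51: √(1 + 12.32/36.75) = 1.156

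**How often the slope rule flags an unbiased IU** (simulation, n = 290, 95% CI for the slope excludes 1, nominal 5%):

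| Setting | Error SD CRL / IU (days) | Flagged |
|---|---|---|
| Separate pre-screening scan sets the window | 1.5/1.5 and 2.0/2.0 | about 5% |
| Same | 1.5/2.13 | about 23% |
| Same | 1.5/3.51 | about 94% |
| Analysed CRL itself sets the window | 1.5/1.5 to 2.0/2.0 | 82% to 97% |
| CRL error-free | 0/2.13 to 0/3.51 | 84% to over 99% |

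**Masking.** With true slope 0.85, IU error SD 3.2 days and an error-free CRL, RMAR slope = √(0.85² + 3.2²/36.75) = √(0.7225 + 0.2786) = 1.00. The rule flagged this in about 4% of runs.

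**Objectives 2 and 3.** With variance 98²/12 = 800.3 and an error-free reference, the slope is √(1 + 4.54/800.3) = 1.003 to √(1 + 12.32/800.3) = 1.008. The flag rate at n = 290 is about 10% to 20%.

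**Intercept.**
- With equal error SDs of 1.5 to 2.13 days and a true slope of 1, the intercept's CI half-width is 3.4 to 4.6 days, against 0.24 to 0.35 days for the mean difference.
- In the same settings the two-step rule finds a fixed bias of 1 day in 5% to 4% of studies, 2 days in 19% to 11%, 3 days in 37% to 21%, 5 days in 78% to 51% and 7 days in 93% to 78%. The mean difference finds 1 day in about 100%.
- With an error-free CRL, IU SD 2.13 and a true bias of +2 days, expected intercept = 2 + 87.5 − 1.06 × 87.5 = −3.25 days, which has the wrong sign.

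**The case against.** The strongest reply has four parts.

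1. **The rate is not known.** The document gives no error SD for either method at 11 to 13 weeks, and it does not settle whether the pre-screening scan supplies the analysed CRL. With a separate scan and equal errors the rule holds its 5%. This stands. A reader might infer that RMAR is bound to declare proportional bias for an unbiased device; the documents do not support that.
2. **RMAR is supplementary.** The mean difference and limits of agreement come first and carry the sample size. This also stands. A reader might infer that the primary agreement estimates are wrong, or that fixed bias goes unmeasured. Neither follows.
3. **Ordinary regression of IU on CRL is no general cure.** With a separate pre-screening scan and equal errors of 1.5 to 2.0 days, its slope is attenuated to about 0.94 to 0.91. It then rejects slope = 1 in roughly 83% to 96% of unbiased studies. This stands and limits the remedy.
4. **Appendix B, said to hold the complete analysis plan, is not shown.** It may add tolerances, centring or an error ratio. That could soften the point, but the rule printed in the article is unconditional and is wrong as a general statement.

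**Conclusion.** The concern holds in a limited form. The slope rule is valid only when the two error variances are equal and the window does not depend on the analysed CRL's error; the protocol ensures neither. For objective 1 at n = 290 the false verdict rate runs from about 5% to over 99% across plausible assumptions, and a true slope of 0.85 can be hidden entirely.

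The intercept rule is very weak for biases of 1 to 3 days and can point the wrong way. It would be too strong to say that it cannot detect fixed bias, since 5 to 7 days is found in 51% to 93% of studies with equal errors of 1.5 to 2.13 days.

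These figures rest on a uniform spread of ages, normal errors, and IU errors borrowed from later gestation. The flaw lies in the supplementary bias reading, chiefly for objective 1.

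**What to change.** - Delete the sentences that read proportional and fixed bias from the RMAR slope and intercept.
- Judge fixed bias by the mean difference and its 95% CI, which are already planned.
- At least for objective 1, assess proportional bias by Deming regression centred within the window, with a stated error-variance ratio and a sensitivity range around it.
- State whether the analysed CRL is the value that sets the 11+0 to 13+6 window. Use ordinary regression of IU on CRL only if it is, or if CRL is explicitly treated as error-free.

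This changes analysis wording only and needs no new data. The cost is that the conclusion on proportional bias then depends on an error-ratio assumption, which is at least visible and can be varied.

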#### Secondary objectives

3. Determine accuracy and precision of gestational age estimation by IU system in second trimester (14^+0^ to 27^+6^ weeks) as compared with fetal biometry by conventional ultrasound in second trimester (14^+0^ to 27^+6^ weeks).

4. Determine the accuracy of identifying women at <20 weeks’ gestation by conventional ultrasound using second trimester fetal biometry, as compared with IU system in second trimester.

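### Objective 4's single detection and false positive rates partly reflect the 14+0 to 27+6 week visit window and do not show how the device classifies women near 20 weeks

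*Protocol article*

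**What the plan says.** The Analysis section of the protocol article says that objective 4 will estimate "the measures of diagnostic performance (specifically the detection rate and the false positive rate) of the IU gestational age estimation approach for classifying individuals as" being under the 20-week cut. The reference and the form of the estimate are given in the same sentence: "compared with conventional ultrasound fetal biometry, both measured at the second trimester, as binomial proportions". It states no breakdown by distance from 20 weeks, and it refers to online supplemental appendix B, which is not at hand, for the complete plan.

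The women who enter these proportions are described under Participant flow and follow-up. "The timing of Visit #2 is generated randomly in REDCap at the end of Visit #1", over the range 14+0 to 27+6 weeks. If the allocated week is missed, "women will be invited to attend at the closest available dates, as long as it is before 28 weeks".

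The only device error given in the article is the in silico result in the Rationale section: a "mean absolute error of 1.7 days between 14 and 18 weeks gestational age and 2.8 days between 18 and 24 weeks".

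**The concern.** The Introduction ties 20 weeks to the start of low-dose aspirin, and objective 4 is the only objective stated at that cut. A reader will take its two rates as the accuracy of the IU system for deciding whether a woman is before or after 20 weeks.

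A detection rate and a false positive rate for a cut on a continuous quantity depend on how far the women lie from the cut. Here the study sets that distance by its choice of visit window. Most women fall well away from 20+0, where even moderate dating error cannot plausibly move them across. They fill both denominators and add almost nothing to the errors. The rates would therefore change with the window even if the device did not, and they say little about a woman who presents at 19 or 20 weeks.

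**Working it through.** **Plan's own figures.** The article gives no figure for objective 4, so the only stated numbers to reproduce are the sample sizes, which supply the counts below. The 95% CI half-width of a limit of agreement, relative to the limit, is √(1/n + 1.96²/(2(n−1))), which is 10.05% at n = 290. Then 290/0.9 = 322.2, rounded up to 323, and 3 × 323 = 969. These agree with the article. With 290 evaluable women per country, the total is 870.

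**Inputs**
- Cut: 20+0 weeks = 140 days (Secondary objectives).
- Visit 2 range: 98 to 196 days, so 42 days below the cut and 56 at or above it (Participant flow and follow-up).
- Error: mean absolute error (MAE) 2.8 days at 18 to 24 weeks (Rationale section). If errors are normal and unbiased, SD = 2.8 × 1.2533 = 3.5 days.
- Assumptions: visit timing is even over the range, and the same SD applies throughout. The article says only that timing is random, and rescheduling will loosen the even spread somewhat.

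**Share of women far from the cut**
- Below 20+0: 1 − 14/42 = 67% are more than 14 days away.
- At or above 20+0: 1 − 14/56 = 75%.
- Fourteen days is 14/3.5 = 4 SD, so these women are almost never misclassified.

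**Pooled rates.** The probability of being called below 20 weeks at reference age g is Φ((140 − g)/SD). Averaging over an even spread gives, to a close approximation:
- missed = 0.399 × SD / (days below the cut)
- false positive = 0.399 × SD / (days above the cut)

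With SD 3.5, 0.399 × SD = 1.4. So missed = 1.4/42 = 3.3% and false positive = 1.4/56 = 2.5%.

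**Same device, other windows** (unbiased, SD 3.5 days)

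| Window | Detection | False positive |
|---|---|---|
| 14+0 to 27+6 (as planned) | 96.7% | 2.5% |
| 16 to 24 weeks (1.4/28 each side) | 95.0% | 5.0% |
| 18+0 to 21+6 (1.4/14 each side) | 90.0% | 10.0% |

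The false positive rate doubles between the first two rows with no change in the device. In the planned window it is lower than the miss rate (2.5% against 3.3%) only because the window is longer above the cut.

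**Response to device error.** At double the error (MAE 5.6 days, SD about 7; an assumption) the pooled rates are 93.3% and 5.0%, and the rates in 18+0 to 21+6 are 80.4% and 19.6%. Over 870 women:
- Pooled: 870 × 42/98 = 373 women below the cut. Misses rise from 12 to 25.
- Band: 870 × 14/98 = 124 women below the cut. Misses rise from 12 to 24.
- Difference between the two devices divided by its standard error: about 2.1 in both cases.

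**Reference error.** The objective 4 reference is second-trimester HC dating. If its SD were 5 days (an assumption), a perfect IU system would still disagree with it in about 0.399 × 5/14 = 14% of women in 18+0 to 21+6. At an SD of 3 days the figure is 0.399 × 3/14 = 9%.

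**The case against.** Several points against the concern stand.

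- **Pooled rates are a legitimate measure.** They cover the declared second-trimester range, and any detection rate depends on case mix. A rate restricted to two weeks each side is just as dependent on its window, and the two-week choice is arbitrary. It should not replace the pooled figures as the headline.
- **Pooled rates do respond to the device.** A reader might infer that they cannot tell a good device from a poor one. The working shows otherwise: doubling the error doubles both error rates, and the band separates the two devices no better. Bias also shows: with SD 3.5 days and a 4-day overestimate, pooled detection falls to 89.9%.
- **Device error is not concealed.** Objectives 2 and 3 report mean differences, limits of agreement and a Bland-Altman plot. An SD of 7 days would appear there as limits of about ±13.7 days.
- **Near the cut, HC error counts against the IU system.** Banded rates against HC alone would make the device look worse than it is.
- **Appendix B may contain more.** It is not at hand and could already include gestational bands.

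What this does not answer is that the Analysis section, as it stands, gives only two proportions for the 20-week question, and neither shows the error near 20 weeks. Limits of agreement allow that error to be worked out only under a model of bias and SD. They do not report it.

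**Conclusion.** The point holds in a limited form. As stated, objective 4's two rates describe the device together with the 14+0 to 27+6 sampling, and they do not show classification near 20+0. At the in silico error the difference is about 96.7% and 2.5% pooled against about 90% and 10% in 18+0 to 21+6. This rests on roughly even visit timing and on unbiased normal error with an SD of about 3.5 days. The mechanism does not depend on the exact SD.

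The documents do not support stronger readings. Women far from the cut have almost no chance of misclassification at this error, which is not the same as none. The statement that a poor device would still score about 93% and 5% needs unbiased error with an SD of about 7 days, which the documents do not give; with a 7-day overestimate as well, pooled detection would be 81.9%. Objective 4 is a secondary objective, so this is a change worth making to the analysis and not a threat to the study's primary results.

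**What to change.** In the Analysis section and appendix B:

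1. Keep the pooled detection and false positive rates. State that they are specific to random visit timing over 14+0 to 27+6 weeks and do not cover women at 28 weeks or later.
2. Add the probability that the IU system calls a woman below 20 weeks as a smooth function of reference gestational age, for example probit or logistic regression on days from 20+0, with 95% CI and using all Visit 2 women. Unlike the proportions, this curve is not set by the width of the visit window.
3. Report the two rates in 18+0 to 21+6 beside it.
4. Show items 2 and 3 also against extrapolated CRL, already defined for objective 2, because HC error inflates apparent misclassification near the cut.

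The cost is a little more analysis and no new data. The band holds about 290 × 4/14 = 83 women per country (870 × 4/14 = 249 overall), half of them below the cut. At 90% detection the 95% half-width is about 1.96 × √(0.09/41) = 9 points per country and 1.96 × √(0.09/124) = 5 points overall. The figures near the cut will also look less favourable than the pooled ones.
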